**Amendments to Statistical Analaysis Plan**

1. The mice procedure needed to be modified to run successfully. We removed randomisation block, intervention arm, whether the leader has SSc, and whether the leader is an experienced versus candidate leader from the list of variables included in the mice procedure, as these variables were collinear with other variables included in the mice procedure. We also did not use the ‘where’ option to account for non-applicable responses, as this was not possible after removing these variables from the mice procedure. Instead, we re-set non-applicable values to ‘NA’ after the mice procedure was completed.
2. For the primary outcome (SGLSS scores immediately post-intervention), the intended analytical models did not converge. Thus, these analysis models were simplified to remove random slopes and to only include a single random intercept for each separate intervention group and for all waitlist participants combined (i.e., not separated by randomisation block) to facilitate convergence.

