**Sample Size**

We identified several meta-analyses that have evaluated self-efficacy in terms of knowledge acquisition and confidence in implementing skills acquired in training programs. A 2016 Cochrane review reported a standardized mean difference effect size of 0.87 for 4 educational interventions designed to change knowledge of sickle cell disease among patients and caregivers (standardized mean difference = 1.12 with an outlier study removed).^1^ Several other similarly focused meta-analyses have reported effect sizes of between 0.58 and 0.94.^2-5^ In the SPIN-SSLED non-randomised feasibility trial, which only included 10 participants, the pre-post change in self-efficacy for carrying out leadership tasks was 1.7 standard deviations.^6^ For an assumed effect size of 0.70, a two-tailed test with α = 0.05, and an intra-class correlation coefficient (ICC) of 0.05, N = 75 would provide ≥ 80% power for self-efficacy for carrying out leader tasks. There was no loss to follow-up in our feasibility trial. Assuming 20% loss to follow-up in the proposed trial, we would need to randomise 94 support group leaders. We believe that this is a conservative power and sample size estimate. First, based on existing systematic reviews and on results of our feasibility trial, we believe that the true effect size is likely larger than 0.70. Second, in cluster RCTs, ICC values for individual patient outcomes are typically lower than our 0.05 estimate, even when different interveners are involved,^7-9^ and we will use the same trainer across groups in each language. If the true ICC is lower than our 0.05 estimate, this will result in greater power than estimated. Third, there was no loss to follow-up in our feasibility trial, and in our previous completed studies in SSc that required follow-up, loss to follow-up has been 10% or less.^10,11^

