1. Trial outcomes will be assessed pre-randomisation, immediately following the 13-week intervention, and 3 months after the end of the intervention period for both participants randomised to the intervention and participants randomised to waitlist.

All analyses will be conducted in R, and will be 2-sided, using an alpha value of 0.05. There will be no adjustment for the multiplicity of secondary outcomes.

For the primary outcome analysis (SGLSS post-intervention), we will use an intent-to-treat analysis that compares all participants randomly assigned to the SPIN-SSLED Program to all participants randomly assigned to the waitlist control. The intervention effect immediately post-intervention will be estimated using a linear mixed-effects model (using the lmer function in lme4),^16^ including baseline SGLSS scores as a fixed effect. To account for the clustering inherent to the blocked PN-RCT design, we will fit a random intercept and slope for intervention by randomisation block and an additional random slope for intervention-by-intervention cluster (i.e., participants in the intervention arm who were in a trial group with the same group leader).^17^

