We will account for missing data by using multiple imputation by chained equations, using the mice package.^18^ We will generate 20 imputed datasets, using 15 cycles per dataset. Variables in the mice procedure will include: randomisation block, trial arm, number of intervention sessions attended, measures of all primary and secondary outcomes at all three assessment time points (baseline, post-intervention, and 3-months post-intervention), age, sex (female vs. male), years of education, living in a city or town (vs. suburb or rural), married or living as married vs. single, currently working full-time or part-time (vs. not currently working), Country (USA, Canada, UK, New Zealand, Australia, or Other), language of instruction (English vs. French), race/ethnicity (White, Black, Hispanic/Latino, or Other), whether the leader has SSc, diffuse vs. limited disease subtype (among those with SSc only), years since SSc diagnosis (among those with SSc only), whether the leader is an experienced (i.e., already leading a support group at the time of trial enrolment) vs. candidate (i.e., identified by a partner organization as intending to initiate a new support group) leader, years as a SSc support group leader (among experienced leaders only), whether leader works with a co-leader (among experienced leaders only), and whether the leader was formerly a member of their support group (among experienced leaders only). We will account for non-applicable responses (e.g., SSc related variables among participants without SSc) by using the “where” option in the mice package. For all outcome measures, we will use total scores rather than item scores, with one exception; for VSI scores at baseline, we will use the 7 items separately. This is because, due to a programming error at the beginning of the trial, several participants only completed 6 of the 7 items. Pooled standard errors and associated confidence intervals will be estimated using Rubin’s rules.^19^

1. As a secondary analysis of the SGLSS, we will also control for age (years), sex (male vs. female), whether the leader has SSc (no vs. yes), and whether the leader is an experienced leader candidate leader as fixed effects.

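### Trial arm was left out of the imputation model, so the arm effect is expected to be attenuated, by an amount the SAP does not allow one to fix

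*SAP*

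**What the plan says.** In the SAP's section on data preparation and analysis, the imputation variables begin with "randomisation block, trial arm, number of intervention sessions attended, measures of all primary and secondary outcomes", and the outcomes enter at all three assessments. Trial arm was therefore part of the plan.

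Item 1 of the amendments section describes what was run: "We removed randomisation block, intervention arm, whether the leader has SSc, and whether the leader is an experienced versus candidate leader from the list". The reason given is collinearity with other listed variables, which are not named. Sessions attended is not among the variables removed, and neither are the outcome scores. Values that do not apply to a participant were set back to missing once the imputation had finished.

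The primary analysis compares all randomised participants by arm, adjusted for baseline score. Secondary outcomes are analysed in the same way. The SAP describes no analysis with arm restored, no imputation by arm and no complete-case check. It does not say how sessions attended was recorded for the waitlist.

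**The concern.** An imputation model should contain every variable in the analysis model, above all the one whose effect is estimated. If it does not, the two models are uncongenial: missing outcomes are drawn as if arm made no difference, except where another variable stands in for arm. Mixing such values with observed ones pulls the arms together.

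After the amendment, the main stand-in is sessions attended, a post-randomisation variable. A second, partial one is a score observed at the other follow-up. If sessions is 0 for the waitlist, intervention participants who attended few sessions are imputed as resembling the waitlist. At stake are the intention-to-treat estimates for the primary and every secondary outcome, and the coverage of their confidence intervals.

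**Working it through.** **Inputs from the SAP.** Analysis: "All analyses will be conducted in R, and will be 2-sided, using an alpha value of 0.05". Primary planning values: "For an assumed effect size of 0.70, a two-tailed test" and "an intra-class correlation coefficient (ICC) of 0.05"; "N = 75 would provide ≥ 80% power for self-efficacy for carrying out leader tasks". Loss: "Assuming 20% loss to follow-up in the proposed trial, we would need to randomise 94 support group leaders". For earlier studies by the same group, "loss to follow-up has been 10% or less". Planned size is 180, or 90 per arm, in training groups of 6. The secondary outcomes use an effect of 0.50.

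**1. The plan's own figure.** The design effect is 1 + (6 − 1) × 0.05 = 1.25 in the intervention arm only, so the average is (1.25 + 1)/2 = 1.125. The unclustered t-test total for 0.70 is 66.05, and 66.05 × 1.125 = 74.3, which rounds up to 75. Then 75/0.8 = 93.75, or 94. Both figures reproduce, so 0.70 and 20% are sound reference values.

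**2. No arm information, closed form.** Let d be the true difference and p the missing share, equal in both arms. Imputed values then have the same expected level in both arms, so only the observed share carries the difference:

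estimate ≈ d × (1 − p)

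- 0.70 × 0.9 = 0.63 and 0.70 × 0.8 = 0.56
- 0.50 × 0.9 = 0.45 and 0.50 × 0.8 = 0.40

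**3. Simulation when benefit does not depend on attendance.** There were 90 participants per arm, true difference 0.70, baseline-outcome correlation 0.5, equal missingness in both arms, predictive mean matching, Rubin's rules and a baseline-adjusted arm effect. The correlation, the 13 sessions and the attendance levels are assumptions. Clustering was not simulated. Each setting used 10 imputations and 150 to 300 replicates, with Monte Carlo standard errors up to 0.010.

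| Imputation model | 10% missing | 20% missing |
|---|---|---|
| Arm included | 0.69–0.70 | 0.69–0.71 |
| No arm, no stand-in | 0.63–0.64 | 0.56–0.57 |
| Sessions, 0 in waitlist; attendance unrelated to missingness | 0.69 | 0.69 |
| Sessions, 0 in waitlist; dropouts attended little (mean 13 × 0.2 = 2.6) | 0.64 | 0.59 |
| Sessions not applicable in waitlist, hence imputed | 0.56–0.65 | 0.42–0.54 |

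With dropouts at a mean of 4 sessions and completers at 11, the fourth row becomes about 0.66 and 0.60. The lowest coverage of the 95% interval was 63%, in the last row at 20%.

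**4. When benefit is proportional to attendance** (means 11, 4 and 0; 20% missing). The amended model, with sessions but no arm, gave 0.69 against 0.69 from full data. Arm without sessions gave 0.80 to 0.81 against 0.70. Arithmetic agrees: mean attendance in the intervention arm is 0.8 × 11 + 0.2 × 4 = 9.6, completers benefit by 0.70 × 11/9.6 = 0.80, and that value is then given to everyone. At 10% missing, arm without sessions gave 0.73 against 0.68. Arm and sessions together gave 0.68 against 0.70 at 20%.

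**5. Scale for the secondary outcomes.** With 90 × 0.8 = 72 completers per arm, the standard error is √((1.25 + 1)/72) = 0.177. Nominal power is 81% for 0.50 and about 62% for 0.40. This holds the standard error fixed and moves only the mean, so it is a rough guide to the worst no-information case at 20% loss.

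**The case against.** The strongest reply is that the SAP does not show any material bias. Sessions attended stayed in the model. If it was 0 for the waitlist, it nearly identifies arm, and when attendance is unrelated to missingness the estimate is 0.69. If benefit follows attendance, pulling low attenders toward the waitlist is right for a comparison of all randomised participants. Scores at the other follow-up also help: with half of the non-responders seen at 3 months, the no-arm estimate at 20% missing was 0.59 against 0.69, rather than 0.55. Loss may be well under 20%, since the SAP reports none in its feasibility trial. Attenuation also does not create a false claim of benefit.

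All of this stands as to size. It does not defend the choice. The benign outcome needs a particular coding plus a particular relation between attendance and missingness or benefit, and the SAP states none of these. Collinearity between arm and sessions is no reason to lose arm, since imputing within arm avoids it.

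A reader might go further and infer three things that the documents do not support:

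- **The effect is understated by a fifth.** That requires 20% missing and no arm information. The SAP gives no missing counts, and scores and sessions remained in the model.
- **Sessions was itself imputed for the waitlist.** Resetting non-applicable values afterwards hints at this, but the SAP does not say that sessions was among them.
- **Restoring arm always removes the bias.** Step 4 shows that it does not if sessions is dropped in exchange.

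**Conclusion.** The point holds as a fault in the procedure as run. The imputation model omits the analysed exposure, and the effect is expected to be attenuated. No simulated setting without arm inflated it.

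The size is not determined. For a true 0.70 it ranges from negligible, through about 0.66 and 0.60 at 10% and 20% missing (sessions 0 in the waitlist, dropouts attending little, benefit unrelated to attendance), to about 0.63 and 0.56 with no arm information. If sessions was treated as not applicable and imputed, it could be lower still. These figures rest on an assumed correlation of 0.5, equal missingness in the two arms, assumed attendance and no clustering. Confidence is high on the fault and low on its size in this trial.

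**What to change.** Run the imputation separately within each arm, with sessions attended as a predictor only in the intervention arm. To the same end, keep arm and sessions together in one model, with sessions set to 0 for the waitlist. Do not restore arm by deleting sessions: if benefit depends on attendance, that overstates the effect (0.80 to 0.81 against 0.70 in step 4).

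Then repeat the 20 imputations and every pooled primary and secondary analysis, including the standardized differences. Report the number of missing outcomes by arm and time point, and how sessions attended was coded for the waitlist in the imputation already run.

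The cost is revised SAP wording and one re-run. Imputation within arm fits each model on about 90 participants, so the list of auxiliary variables may have to be shortened.

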2. Analyses of secondary outcomes will similarly be done (1) controlling for baseline scores only and (2) controlling for baseline scores and additional covariates. However, OLBI and VSI were only collected and will only be assessed among experienced leaders, since they are not relevant to candidate leaders. Thus, these analyses will not include leader experience as an additional covariate.
3. To aid in the interpretation of study results, for primary and secondary outcomes, post-intervention and 3 months post-intervention, we will produce model-adjusted standardized mean differences (Hedges’ g), using an adapted version of the method proposed by Borenstein and Hedges.^20^ For each outcome and time point, we will calculate the associated Hedges’ g estimate by dividing the unstandardized regression coefficient for the intervention effect by the unadjusted standard deviation of the outcome variable. To produce standard errors, we will use formula 11.31 from Borenstein and Hedges, which incorporates an estimate of the proportion of unexplained variance in the model (i.e., “1 - R^2^” in a standard linear regression model).^20^ In our case, we will estimate this proportion by dividing the estimated residual variance from the model by the unadjusted variance of the outcome variable. Estimated Hedges’ g and associated standard errors will be computed in each imputed dataset and then results will be pooled across imputed datasets using Rubin’s rules.^19^ Since the Borenstein and Hedges formula was not designed for the PN-RCT but was adapted, it approximates Hedges’ g and 95% CI.

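### The amended imputation leaves out leader status and SSc status, although the adjusted models use both as covariates

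*SAP*

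**What the plan says.** The section Data Preparation and Analysis sets out the imputation: "We will account for missing data by using multiple imputation by chained equations, using the mice package". It adds "We will generate 20 imputed datasets, using 15 cycles per dataset". The variable list includes "measures of all primary and secondary outcomes at all three assessment time points (baseline, post-intervention, and 3-months post-intervention"), with the seven baseline VSI items entered separately. It also includes fields defined only for a subgroup: "years as a SSc support group leader (among experienced leaders only), whether leader works with a co-leader (among experienced leaders only") and former membership of the group, and "diffuse vs. limited disease subtype (among those with SSc only), years since SSc diagnosis (among those with SSc only"). Leader status and SSc status were on the list, and `where` was to keep non-applicable cells from being imputed.

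In the secondary SGLSS analysis, "we will also control for age (years), sex (male vs. female), whether the leader has SSc (no vs. yes"), and also for experienced versus candidate status. Secondary outcomes follow the same pattern. OLBI and VSI were collected only in experienced leaders, "since they are not relevant to candidate leaders", so leader experience drops out of those two models. It stays in the PHQ-8 model, and SSc status stays in all of them.

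Item 1 of the amendments then removes block, arm, SSc status and leader status from mice, citing collinearity. It drops the `where` "option to account for non-applicable responses, as this was not possible after removing these variables from the mice procedure", and returns non-applicable cells to missing only once mice has finished.

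**The concern.** An imputation model should contain every variable in the analysis model. If a covariate is left out, imputed values do not carry its association with the outcome. Here, two people with the same values on the other variables get the same predictive distribution for a missing SGLSS or PHQ-8 score, even if one leads a group and the other does not. The adjusted model then estimates a leader-status effect from data in which part of that effect has been removed. If dropout depends on status differently in the two arms, the arm comparison can shift as well.

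The secondary matter is the non-applicable cells. Without `where`, mice gives candidates burnout, satisfaction and leader-history values, and gives participants without SSc a disease subtype and a time since diagnosis. Returning these cells to missing afterwards keeps them out of the final data, but they may already have served as predictors for real missing values.

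**Working it through.** The SAP states no figure on this point, so there is none to reproduce.

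**Which models are affected**

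| Adjusted model | Leader status: covariate / in amended mice | SSc status: covariate / in amended mice |
|---|---|---|
| SGLSS | yes / no | yes / no |
| PHQ-8 | yes / no | yes / no |
| OLBI, VSI | no / no | yes / no |

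**Non-applicable fields.** Each candidate has OLBI at 3 times, VSI as 7 baseline items plus 2 follow-up totals, and 3 leader-history fields: 3 + 9 + 3 = 15. Each participant without SSc has 2.

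**Assumed inputs (not in the SAP).** Candidates are 30% of participants and score 0.5 SD lower given baseline. The arm effect is 0.50 SD. Arm is kept in the imputation, to isolate this point.

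**Case 1: 20% missing everywhere.**
- Imputed values centre on 0.30 × (-0.50) = -0.15 relative to experienced leaders.
- Candidate mean: 0.8 × (-0.50) + 0.2 × (-0.15) = -0.43.
- Experienced mean: 0.8 × 0 + 0.2 × (-0.15) = -0.03.
- Status coefficient: -0.43 - (-0.03) = -0.40. In general it is -0.50 × (1 - m) for a uniform missing fraction m, so -0.45 at 10%.
- Both arms shift equally, so the arm effect stays at 0.50.

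**Case 2: 40% missing among intervention candidates, 10% elsewhere.** Within each arm the imputed mean equals the observed mean, so the shift is 0.50 × (candidate share among observed controls - candidate share among observed intervention participants).
- Intervention: 0.30 × 0.60 = 0.18 and 0.70 × 0.90 = 0.63, so the share is 0.18 / 0.81 = 0.222.
- Control: the share stays at 0.30.
- Shift: 0.50 × (0.300 - 0.222) = 0.039, so 0.50 becomes 0.54.
- With 30% in place of 40%: share 0.21 / 0.84 = 0.250, shift 0.025. With 50%: share 0.15 / 0.78 = 0.192, shift 0.054.

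If status is balanced between arms, this shift is the same with or without status in the analysis model. The baseline-only SGLSS analysis would then be exposed too.

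**Simulation of the amended scheme** (N = 180, 60% or 80% experienced, more missing data in candidates in both arms, arm kept). Removing status and filling non-applicable cells together moved the status coefficient from 0.50 (here experienced minus candidate) to 0.43 to 0.45 at 10% nominal missingness, and to 0.36 to 0.38 at 20%. With status included and the subgroup-only fields left out, it was 0.49 to 0.51. The arm effect moved by 0.005 or less.

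**The two features separated** (N = 180, 30% candidates, three subgroup-only auxiliaries, 400 replicates, Monte Carlo standard error 0.007 for the arm effect). Each pair is without / with filling of non-applicable cells.

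| | Arm effect, 20% missing everywhere | Arm effect, 40% vs 10% | Status coefficient, 20% missing everywhere |
|---|---|---|---|
| Status in imputation | 0.497 / 0.498 | 0.513 / 0.506 | -0.51 / -0.49 |
| Status left out | 0.495 / 0.505 | 0.540 / 0.536 | -0.39 / -0.40 |

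Omitting status accounts for essentially all of the attenuation. Filling makes no detectable difference.

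**The case against.** The strongest reply is that the trial's target is hardly touched. The SAP estimates the intervention effect. Leader status is a nuisance covariate in a secondary model, and the primary model adjusts for baseline SGLSS only. The arm effect is unbiased under uniform missingness, and close to unbiased when candidates drop out more in both arms alike. The 0.04 shift needs a particular pattern of dropout and a 0.5 SD candidate deficit, and the SAP supports neither. Its Sample Size section reports no loss in the feasibility trial and 10% or less in earlier studies. Against a simulated standard deviation of 0.13 to 0.14 for the estimate, 0.04 is about 0.3 of a standard deviation. All of this stands, and it limits the weight of the point.

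A reader might also infer that invented burnout and leader-history values have contaminated the results. The documents do not support that. The SAP gives no predictor matrix, so the use of these cells as predictors is likely but not stated. The reset keeps them out of the OLBI and VSI analyses. The separated simulation showed no detectable bias from filling, although it used only three auxiliaries and simple linear models.

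Collinearity was a real obstacle, since leader status does not vary among people with observed OLBI or VSI. That does not justify the choice made. The fields undefined for a subgroup could have been left out instead of covariates known for everyone. Nor is the reason for dropping `where` convincing: the later reset shows that the non-applicable cells could be identified from data held outside the imputation.

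**Conclusion.** The point holds as a mismatch between imputation and analysis. Leader status and SSc status are missing from the amended imputation but present in the adjusted SGLSS and PHQ-8 models, and SSc status in the adjusted OLBI and VSI models. It should be corrected because correction is cheap, not because a large bias is shown.

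The size rests on assumptions throughout: the SAP does not give the candidate share, the outcome gap, or dropout by status and arm. With the values above, the status coefficient is attenuated by about a fifth at 20% missing, and the arm effect moves only if dropout differs by status between arms. A reader might go further and conclude that the treatment effect is biased. Nothing in the SAP shows the dropout pattern that this would need.

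The same amendment also removes trial arm from the imputation. That is a separate and probably weightier matter. The figures here keep arm in and say nothing about it.

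**What to change.** Replace the single imputation with two.

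- **(a) SGLSS and PHQ-8, all participants.** Include arm, leader status, SSc status, age, sex and the other variables that apply to everyone. Leave out OLBI, VSI, the leader-history fields and the SSc-detail fields.
- **(b) OLBI and VSI, experienced leaders only.** Include arm, SSc status, age, sex and the leader-history fields. Leave out the SSc-detail fields.

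Neither run then has non-applicable cells, so neither `where` nor a later reset is needed. Some collinearity may remain, because sessions attended is closely tied to arm. If it is collinear with arm or block in either run, drop or recode sessions attended rather than the analysis variables.

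The cost is revised SAP wording and one more mice run. The downside is small: OLBI and VSI no longer serve as auxiliary variables for SGLSS and PHQ-8.

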**SAP Version 1 (2021-06-14)**

**Study Design**

The SPIN-SSLED Trial is a pragmatic, two-arm, parallel, blocked, partially nested randomised controlled trial (PN-RCT). The trial is a blocked PN-RCT because eligible participants will first be grouped into blocks (referred to as “pools” in main text) based on language and scheduling availability, and then randomised into intervention arm. Within each block, participants randomised to the intervention arm will interact with their group facilitator and with others in their group during videoconference sessions. Within each block, participants randomised to the waitlist control arm will not interact with each other and will only complete trial measures.

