For the secondary outcomes (emotional distress, burnout, leader satisfaction (participation efficacy)), based on published meta-analyses, a standardized mean difference effect size of 0.50 represents a clinically meaningful effect size for improvement that has been achieved in training programs for managers, caregivers of chronically ill patients, and parents of children with difficult behavior.^2,12-14^ This is also considered a clinically meaningful effect size for patient-reported health outcomes, including depressive symptoms.^15^ For effect size = 0.50, a two-tailed test with α = 0.05, and an ICC of 0.05, N = 146 would provide ≥ 80% power for both self-efficacy and patient-reported health outcomes. Assuming 20% loss to follow-up in the proposed trial, we would need to randomise 182 support group leaders. We did not estimate power for leader satisfaction.

Members of our Support Group Leader Advisory Team and our patient organization partners have emphasized the importance of evaluating the trial’s planned secondary outcomes. Thus, we will attempt to enrol 180 participants total (15 training groups of 6 participants; 90 participants in waitlist control) in order to have sufficient power to adequately evaluate secondary outcomes.

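### The amended primary model gives the whole waitlist arm one shared random intercept, which inflates the standard error of the intervention effect (1.75-fold at the plan's ICC of 0.05) and loses the stated 80% power

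*SAP*

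**What the plan says.** The Study Design section describes a partially nested trial. Intervention participants meet in training groups, while "participants randomised to the waitlist control arm will not interact with each other and will only complete trial measures". The original primary model (Data Preparation and Analysis) followed this design: a random intercept and intervention slope by randomisation block, plus an intervention effect varying by training group.

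Item 2 of the amendments replaces it: "For the primary outcome (SGLSS scores immediately post-intervention), the intended analytical models did not converge". The random slopes are dropped, and the models now "only include a single random intercept for each separate intervention group and for all waitlist participants combined". On the planned layout this is one grouping factor with 16 levels: 15 training groups and one level holding all 90 waitlist participants. The only reason given is convergence. Standard error and power are not discussed.

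The Sample Size section makes two power claims that cover self-efficacy, both at a two-sided alpha and an ICC of 0.05 each:

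- At an effect of 0.70 the claim is that "N = 75 would provide ≥ 80% power for self-efficacy for carrying out leader tasks".
- At an effect of 0.50 the claim is that "N = 146 would provide ≥ 80% power for both self-efficacy and patient-reported health outcomes".

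The target is 180 participants: 15 training groups of 6, and 90 on the waitlist.

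**The concern.** A random intercept represents a shared influence that differs from cluster to cluster. Training groups can have one; people who do not interact cannot. Putting the whole waitlist arm in one cluster tells the model that the waitlist mean carries its own random shift, with the same variance as the shift between training groups.

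The arm has only one such cluster, so that shift cannot be told apart from the arm effect. The data cannot estimate it, yet the model still charges its full variance to the intervention effect. Recruiting more waitlist participants does not reduce this term.

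At stake are the confidence interval and p-value of the primary outcome. A programme that works as well as planned could be reported as inconclusive.

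**Working it through.** **Inputs from the SAP.** Effects of 0.70 and 0.50 SD; two-sided alpha 0.05; ICC 0.05; 15 groups of 6; 90 waitlist; 20% loss to follow-up. **Assumptions.** Outcome SD 1, so between-group variance τ² = ICC and residual variance σ² = 1 − ICC; no gain from baseline adjustment (the SAP's power statement mentions none); REML, the lmer default; Wald z test; complete data.

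**1. The plan's own sample sizes.** A two-sample t-test with 80% power needs 33.02 per arm at 0.70 and 63.77 at 0.50. The design effect is 1 + (6 − 1) × 0.05 = 1.25 in the intervention arm and 1.00 in the waitlist arm, average 1.125.

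- 0.70: 2 × 33.02 × 1.125 = 74.3, so 75 (stated 75). With loss, 75/0.8 = 93.75, so 94 (stated 94).
- 0.50: 2 × 63.77 × 1.125 = 143.5, so 144 (stated 146).
- Clustering in both arms would give 83 and 160, which do not match.

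The sample size therefore counts clustering in the intervention arm only.

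**2. Why the extra term appears.** The waitlist indicator equals the intercept column minus the arm column, so it lies in the space of the fixed effects. Under REML the lone waitlist intercept drops out of the likelihood. Variance estimates and the point estimate equal those of the partially nested model. Only the variance of the arm effect changes, and it rises by exactly τ²:

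- Partially nested: τ²/15 + σ²/90 + σ²/90
- Amended: τ²/15 + τ² + σ²/90 + σ²/90

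**3. At ICC 0.05.**

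- Partially nested: 0.05/15 + 0.95 × 2/90 = 0.0244; SE 0.156.
- Amended: 0.05 × 16/15 + 0.95 × 2/90 = 0.0744; SE 0.273.
- Ratio 0.273/0.156 = 1.75. However many participants are added to the waitlist, the amended SE cannot fall below √0.05 = 0.22.

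With these variances treated as known, power is Φ(effect/SE − 1.96). For the amended model this gives Φ(0.70/0.273 − 1.96) = 73% and Φ(0.50/0.273 − 1.96) = 45%.

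**4. With variances estimated by REML (simulation, 15 × 6 against 90).**

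| True ICC | SE ratio, variances known | Median ratio across fits | Amended power at 0.50 | Amended power at 0.70 |
|---|---|---|---|---|
| 0 | 1.00 | 1.00 | 71% | 89% |
| 0.02 | 1.37 | 1.24 | 62–63% | 84% |
| 0.05 | 1.75 | 1.65 | 50% | 73% |
| 0.10 | 2.18 | 2.11 | 32% | 55% |

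At ICC 0.05 the partially nested model has 89% power at 0.50 and 99% at 0.70. The type I error of the amended model is 2.3%, against about 5% for the partially nested one. About 29% of fits estimate τ² as zero and show no inflation. Power is lost even at a true ICC of 0 because τ² is often estimated above zero.

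**5. Other sizes at ICC 0.05.** After 20% loss (72 per arm), the ratio with known variances is about 1.62–1.64. Simulated power is about 70% against 98% at 0.70, and 47% against 82% at 0.50. At N = 75, the size quoted for 0.70, the ratio is about 1.35 and power about 57%.

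**The case against.** The algebra is not in dispute; its reach is.

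- **The ratio is conditional.** 1.75 holds at an ICC of exactly 0.05, which the SAP itself calls conservative. At 0.05 the median realised ratio is 1.65; at 0.02 it is 1.24. This stands and limits the size.
- **Power at 0.70 is not always lost.** With all 180 retained, simulated power is still 80% at ICC 0.03. This stands. It does not help at 0.50, where the SAP also claims 80% power for self-efficacy and the amended model misses it at every ICC tried.
- **Baseline adjustment is ignored.** With an assumed baseline correlation of 0.5 (the SAP gives none), amended power at ICC 0.05 is 78–83% at 0.70 and 53–60% at 0.50, depending on whether the adjustment also shrinks the between-group variance. It can make up part of the loss, but it does not remove the added term.
- **The error is conservative.** The type I error stays below 5%, so no false claim of benefit results. This is true, but the primary interval and p-value still do not fit the design.
- **Scope.** Item 2 names only the primary outcome. The Hedges' g interval uses a formula based on residual variance, so the inflation described here concerns the unstandardised coefficient. Both points stand.
- **A second data-dependent change.** Models had already been fitted to outcome data, and the remedy gives a smaller standard error. This is a fair caution. The case for the change rests on the design and on algebra that holds before any data are seen, and reporting both results answers the rest.

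**Conclusion.** The amended random-effects structure is wrong as written. It contradicts the partially nested design, the original model and the sample size, all of which place clustering in the intervention arm only. It adds the full between-group variance to the variance of the primary effect.

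At the plan's ICC of 0.05 and full enrolment the standard error is 1.75 times too large. Power is 73% at 0.70 and 50% at 0.50, where a correctly specified model has 99% and 89%. The inflation would be smaller at a lower ICC and larger at a higher one. These figures assume REML, a Wald z test, complete data and no baseline gain; Satterthwaite degrees of freedom would lower amended power further. Because the primary inference is affected and the remedy is cheap, this must be fixed.

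**What to change.** Amend item 2 so that the group effect exists only in the intervention arm. With arm coded 0/1, use (0 + arm | training group) in lmer. Waitlist participants may carry any group label, because their arm value of 0 removes the effect. Apply this to both primary-outcome models, the one adjusted for baseline only and the one with added covariates.

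Report the single-waitlist-cluster result beside it as a sensitivity analysis. State that the change was made after the first models had been fitted and that the reason is structural. The replacement, like the amended model, leaves out the randomisation block, and the SAP should say so.

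The cost is one line of model code and a SAP amendment. There is still one between-group variance parameter and the REML likelihood is the same, so convergence should be no harder.
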